## Abstract

Background: Obsessive-compulsive disorder (OCD) is a complex condition marked by persistent distressing thoughts and repetitive behaviours. Despite its prevalence, the mechanisms behind OCD remain elusive, and current treatments are limited. This protocol outlines an investigative study for individuals with OCD, exploring the potential of psilocybin to improve key components of cognition implicated in the disorder. The PsilOCD study strives to assess the effects of low-moderate psilocybin treatment (10 mg) alongside non-interventional therapy on several facets of OCD. The main focus points of PsilOCD are cognitive flexibility, measured with cognitive tests, and neuroplasticity, assessed through electroencephalography (EEG).

Methods: 20 blinded participants with OCD will complete two dosing sessions, separated by four weeks, where they will receive 1 mg of psilocybin on the first and 10 mg on the second. The first dose serves as an active placebo, and the latter is a low-moderate dose that induces relatively mild-moderate emotional and perceptual effects. Participants will be supported by trained psychedelic therapists, who will sit with them during each dosing session and provide virtual preparation and integration sessions over the 12-week study period. Therapeutic support will be the same for both the 1 mg and 10 mg sessions. PsilOCD’s primary outcomes include scores in the intradimensional-extradimensional (ID-ED) shift task, which is an established measure of cognitive flexibility, and neuroplasticity as quantified by a visual long-term potentiation (vLTP) task. This task is delivered as part of an EEG paradigm and measures acute quantified changes in neuroplasticity in the brain’s visual system. The ID-ED task will be conducted twice, two days after each dosing session, and the EEG recordings will also be taken twice, immediately after each session. Secondary outcome assessments will include OCD and affective symptom severity, as well as an array of patient-reported outcome measures (PROMs), in the form of questionnaires designed to assess well-being, dissociable and well-established mood-related (affective) measures, and participants’ subjective experience of the psilocybin experience.

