Participants will complete study activities at 13 time points over the 12-week study period after screening, of which two are in-person dosing days (see Figure 1 for the schedule). Two trained therapists (or ‘guides’) will accompany participants and provide psychotherapeutic support throughout the duration of the study (more information in the section below). Participants will attend two dosing days and receive 1 mg of psilocybin on the first (active placebo) and 10 mg on the second. Dosing sessions are separated by at least four weeks, each preceded by at least one preparation session and followed by four integration sessions, with the final integration session coming four weeks after the final dosing session.

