**Table 2 TAB2:** Summary of PsilOCD Outcome Measures and Hypotheses ID: Intradimensional; ED: Extradimensional; CANTAB: Cambridge Neuropsychological Test Automated Battery; EEG: Electroencephalography; vLTP: Visual long-term potentiation; Y-BOCS: Yale-Brown Obsessive Compulsive Scale; MADRS: Montgomery-Asberg Depression Rating Scale; PROM: Patient-reported outcome measure; BDNF: Brain-derived neurotrophic factor

Outcome Type	Outcome Measure	Hypothesis
Primary Clinical Outcome	Cognitive Flexibility: ID-ED Shifting (CANTAB)	Participants will show improved scores on the CANTAB ID-ED task two days after the 10 mg psilocybin dose compared to two days after the 1 mg dose.
Primary Neuroimaging Outcome	Neuroplasticity: EEG vLTP	Participants will demonstrate higher capacity for neural plasticity two hours post 10 mg dose compared to the 1 mg dose, as indicated by vLTP in EEG recordings.
Secondary Clinical Outcome	Y-BOCS and MADRS Scores	Y-BOCS scores for obsessions and compulsions are expected to decrease after the 10 mg dose but not after the 1 mg dose. MADRS scores will likely follow a similar pattern.
Secondary Clinical Outcome	Cognitive Inflexibility: Reversal Learning (CANTAB)	Participants will show improved scores in reversal learning two days post 10 mg psilocybin dose, but not two days post 1 mg dose.
Secondary Clinical Outcome	Cognitive Inflexibility: Paired Associates Task (CANTAB, Control Task)	Scores are expected to be comparable after both 1 mg and 10 mg doses, as visuospatial tasks should not be affected by 5-HT2A receptor modulation.
Secondary Clinical Outcome	Cognitive Inflexibility: Information-Seeking Task	If psilocybin reduces the rigidity of high-level priors, confidence will improve, and information-seeking behavior will reduce. Significant effects are expected one day after the 10 mg dose, not the 1 mg dose.
Secondary Clinical Outcome	Self-Reported Well-Being and Affective Measures (PROMs)	Compared to 1 mg, the 10 mg dose is expected to improve anxiety and depression-related symptoms, decrease impulsivity (Barratt Impulsivity Scale), increase openness, and decrease neuroticism (Big Five Inventory).
Secondary Clinical Outcome	Acute Subjective Experiential Measures (PROMs)	The 10 mg psilocybin dose will result in significantly higher scores on questionnaires assessing subjective drug effects compared to the 1 mg dose.

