Secondary Clinical Outcome	Blood Analysis: Serum BDNF and Plasma Inflammatory Markers	The 10 mg dose, but not the 1 mg dose, will significantly increase serum BDNF levels and reduce plasma markers of inflammation. This outcome is exploratory and focuses on psilocybin's potential acute anti-inflammatory effects.

Mechanistic neurophysiology outcome measures

In order to ascertain the effect of this low dose of psilocybin on neuroplasticity in an OCD population, the vLTP EEG paradigm will be run at three time points during the course of the study. The first EEG session takes place during the in-person screening day to acquire baseline recordings, while the subsequent two are done on both dosing days after the effects of the drug have worn off (two hours after dosing).

The vLTP paradigm uses tetanising visual stimulation to measure the brain's capacity to undergo neuronal plasticity, specifically in the occipital lobe where we can easily measure evoked responses to external visual stimuli. This vLTP paradigm was developed at the University of Auckland and is now incorporated into several psychedelic trials both at the University of Auckland and Imperial College London. As the vLTP paradigm quantifies neuroplasticity, this will provide valuable insight into whether psilocybin enhances it in OCD patients.

Cognitive tasks

As cognitive inflexibility is a hallmark characteristic of OCD and potentially causal to the onset of symptoms, we are investigating it through several cognitive tasks. The first, the ID-ED task, is delivered as part of the CANTAB; it measures participants’ ability to switch their focus from one dimension of a task (set of stimuli) to another. The reversal-learning task, also part of the CANTAB, assesses their ability to learn to no longer apply a rule when it becomes obsolete. The final CANTAB task, the visuospatial paired-associates task, serves as a control and will indicate the order effect at play. Scores are not expected to be influenced by psilocybin. The information-seeking task developed by Schulz et al. measures participants’ tendency to seek extra information, assessing confidence and decision-making [79].

Patient-reported outcome measures

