Visit #			-	V1	V2	V3	V4		V5		V6	V7	V8	V9	V10	V11	V12	V13	V14	V15
Visit Name			Video Screening	In-Person Screening	Prep 1	Prep 2	Dose 1		1DFU1		CANTAB	1WFU1	2WFU1	1MFU1 / Prep-3	Dose 2	1DFU2	CANTAB	1WFU2	2WFU2	1MFU2
Day			At least 2W from V4	At least 2W from V4	D-1 (>1W pre V4)	D-7 (>1D pre V4)	D-8		D-9		D-10	D-15	D-22	D-34	D-42	D-43	D-44	D-49	D-56	D-70
Face-to-Face				X			X								X					
Virtual (Microsoft Teams)					X	X			X		X	X	X	X		X	X	X	X	X
Dosing Days							X								X					
EEG																				
Resting State (Eyes Closed)				X			X								X					
Resting State (Eyes Open)				X			X								X					
vLTP				X			X								X					
MMN				X			X								X					
Clinician-Rated Scales																				
Y-BOCS			X			X						X	X	X				X	X	X
MADRS			X			X						X	X	X				X	X	X
Cognitive Tasks																				
ID-ED Set-Shifting Task											X						X			
Reversal Learning Task											X						X			
Paired-Associates Task											X						X			
Information-Seeking Task											X						X			
Physiological Measures																				
Oura Ring (Data Collected Throughout study)				X	X	X	X		X		X	X	X	X	X	X	X	X	X	X
Blood Analysis																				
BDNF (Plasma Levels)							X								X					
Epigenetic Markers (Plasma Levels)							X								X					
Immune Markers (Plasma Levels)							X								X					
PROMs																				
Obsessionality-Related Outcomes																				
Challenge Y-BOCS							Xba		X						Xba	X				
WBSI					X									X						X
CPAS					X															
CAIOC-13					X									X						X
Affective Outcomes																				
PHQ					X	Xb	(Xb)					X	X	X	(Xb)			X	X	X
BDI						Xb							X	X					X	X
SDS					X							X	X	X				X	X	X
STAI T					X	Xb	(Xb)					X	X	X	(Xb)			X	X	X
STAI S							Xba		X						Xba	X				
BSL-23				X																
BIS					X									X						X
bEAQ					X									X						X
Hybrid Personality Measure					X									X						X
PID-5-FBF					X									X						X
Breaking of Blind Question							Xa								Xa					
Menstrual Cycle-Related Questions (Female Participants)				X	X	X			X			X	X	X		X		X	X	X
Premenstrual Symptoms Screening Tool (Female Participants)				X	X	X			X			X	X	X		X		X	X	X
Acute Subjective Psilocybin Measures																				
Acute State Scales (MEQ, CEQ, EBI)							Xa								Xa					
GEMS, PMQ							Xa								Xa					
PIS									X			X				X		X		

Peripheral physiological data

Physiological data including heart rate variability (HRV), actigraphy, and sleep staging will be collected using Oura Ring devices throughout the study.

Bloods

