Firstly, we intend to summarise essential participant characteristics and scrutinise outcome variables at both time points using descriptive statistics. We will then employ a linear mixed effects model (or equivalent) to assess the impact of 10 mg of psilocybin on Y-BOCS and MADRS scores, allowing us to determine the interaction between time and dose. Alternatively, paired t-tests (or equivalents) will be used to discern mean differences for other outcomes including the ID-ED task, reversal learning task, and information-seeking task. Tests for normality, homoscedasticity, and sphericity (where required) will be performed. We will ascertain effect size (Cohen’s d) and statistical power to gain a more nuanced understanding of the observed differences appropriate for our sample size of 20 completers. Furthermore, we will perform correlation analysis, exploratory factor analysis, and subgroup analyses based on participant characteristics to enrich our interpretations of outcomes. It will be necessary to adjust for baseline covariates and sensitivity analyses. GraphPad Prism, Python, R and MATLAB will be used to carry out the statistical analyses described and to produce appropriate figures such as line plots, scatter plots, and box plots. See Table 4 below for the time points of interest and the statistical plan.

**Table 4 TAB4:** Statistical plan for the main PsilOCD outcomes The purpose of this table is to maintain clarity and transparency regarding the main study outcomes. Additional analyses may be conducted in an exploratory fashion. Paired t-tests and ANOVA assume certain conditions such as normality, homoscedasticity, and, in the case of ANOVA with repeated measures, sphericity. All datasets will undergo testing, and if these assumptions are not met, suitable alternative tests will be employed (for instance, utilising the Welch t-test in place of the standard paired t-test). *First dosing day; **second dosing day. ID: Intradimensional; ED: Extradimensional; CANTAB: Cambridge Neuropsychological Test Automated Battery; LTP: Long-term potentiation; EEG: Electroencephalography; MMN: Mismatch negativity; ANOVA: Analysis of variance; Y-BOCS: Yale-Brown Obsessive Compulsive Scale; MADRS: Montgomery-Asberg Depression Rating Scale; BDNF: Brain-derived neurotrophic factor

Measure	Timepoints for Analysis
Primary Outcome Measures	
ID-ED Set-Shifting Task (CANTAB)	Two days- post 1 mg vs two days post 10 mg (paired t-tests or equivalent)

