## Conclusions

By publishing the study protocol, we aim to improve methodological transparency, rigour, and accountability and subsequently contribute towards more impactful outcomes. This study will investigate the effect of psilocybin on neural mechanisms in an OCD population, representing the first study exploring the impact of psychedelics on OCD in the UK. It is important to note that the small sample size of up to 20 completers, while typical for early-stage feasibility studies, inherently limits the statistical power of the results and, consequently, their generalisability. However, such studies remain invaluable for generating preliminary insights into efficacy and tolerability, identifying patterns in individual responses, and refining hypotheses to guide the design of larger-scale clinical trials.

The results will reveal whether a low-moderate dose of psilocybin improves clinical OCD symptoms, and whether this correlates with changes in the underlying cognitive features of OCD, neuroplasticity levels, BDNF serum levels, and inflammatory mediators. Consequently, the findings from PsilOCD have the potential to evaluate the potential of psilocybin for OCD, inform larger, randomised clinical trials, and, if the results are promising, pave the way for making this treatment accessible to patients.

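### The primary ID-ED comparison estimates dose and test order together: 1 mg always comes first, the task is never given before dosing, and the planned control-task test cannot separate the two

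*Protocol article*

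**What the plan says.** **Order of doses.** Under Study visits, participants "receive 1 mg of psilocybin on the first (active placebo) and 10 mg on the second". No other sequence is described.

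**Timing of the task.** The Abstract states: "The ID-ED task will be conducted twice, two days after each dosing session". Table 3 agrees: the row "ID-ED Set-Shifting Task" is marked only at V6 (D-10, after 1 mg) and V12 (D-44, after 10 mg). Nothing is marked at screening or at the preparation visits.

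**Primary analysis.** For ID-ED, Table 4 gives "Two days- post 1 mg vs two days post 10 mg (paired t-tests or equivalent").

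**Hypothesis.** Table 2 predicts better ID-ED performance following 10 mg than following 1 mg, with each test at two days.

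**Safeguard.** Under Cognitive tasks, "the visuospatial paired-associates task, serves as a control and will indicate the order effect at play". Table 2 expects similar scores on this task after both doses. Table 4 gives it a separate paired t-test, first versus second dosing session.

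**Limitations.** The Conclusions name the small sample. They do not mention the fixed order.

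**The concern.** The 10 mg score is always the second time a participant meets the task. It also comes 34 days later and after more therapist contact. ID-ED tests whether a person detects a change in the relevant dimension, so it is plausible that having met the change once helps the next time, whatever the dose. Such a gain would push the result in the hypothesised direction.

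The article recognises that order may matter, but the one analysis it states for the control task leaves the ID-ED estimate as it is. A positive result on a named primary outcome could then be reported as an effect of 10 mg on cognitive flexibility when the data are equally compatible with repeat testing. A later analysis plan can add contrasts, but it cannot recover a pre-dose score that was never collected.

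**Working it through.** **1. What the contrast estimates.** For each person, let D be the second ID-ED score minus the first, signed so that positive means improvement. Then

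E[D] = dose effect (10 mg versus 1 mg) + order effect (practice, elapsed time, accumulated support).

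Everyone has the same sequence and only two scores, both after dosing. That gives one equation with two unknowns. A larger sample narrows the interval around the sum and does not separate its parts. The general statement in Analysis strategy about adjusting for baseline covariates does not help, because there is no ID-ED baseline.

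**2. Inputs.**
- n = 20 completers (Recruitment; an upper limit).
- Two-sided 5% level: assumed, as the article states none.
- Practice gain in SDs of the paired differences, dz: assumed at 0.3, 0.5 and 0.8, as the article gives no figure.
- The article has no power calculation or effect size for this outcome, so there is no figure of its own to reproduce.

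**3. Rejection rate of the primary test with no drug effect.** Under a pure order effect the paired t statistic is noncentral t with 19 degrees of freedom and noncentrality dz × √20. The critical value is 2.093.

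| Assumed dz | Noncentrality | P(reject) |
|---|---|---|
| 0 | 0 | 0.050 |
| 0.3 | 1.342 | 0.247 |
| 0.5 | 2.236 | 0.565 |
| 0.8 | 3.578 | 0.924 |

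**4. What the control-task t-test can exclude.** The 95% half-width is 2.093/√20 = 0.468 SD of the paired differences. If the observed control change were exactly zero, the interval would still reach 0.47 SD. If it were 0.2 SD, the interval would run from 0.2 − 0.468 = −0.27 to 0.2 + 0.468 = 0.67, which is non-significant and still compatible with a large order effect. The test has 80% power only for an order effect of about 0.66 SD.

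**5. Reading the two tests side by side.** Suppose there is no drug effect and the same practice gain on both tasks. In simulation (100,000 runs), the pattern of ID-ED significant and control not significant occurs as follows.

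| Gain on both tasks (dz) | Differences uncorrelated | Correlation 0.3 |
|---|---|---|
| 0.3 | 0.187 | 0.157 |
| 0.5 | 0.248 | 0.204 |
| 0.8 | 0.069 | 0.062 |

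If the gain is 0.5 on ID-ED but 0.1 on the control task (correlation 0.3), the pattern occurs in 0.514 of trials. Significant on one task and not on the other is not a test of the difference between them.

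**The case against.** - **The authors saw the issue.** They foresaw an order effect and added a neutral control task, which is more than many small studies do. This stands as partial mitigation.
- **No decision rule is stated.** A reader might infer that the plan treats a null control result as proof of no order effect. The article does not say so. It says the task will indicate the order effect, and it predicts similar scores on pharmacological grounds. The supportable criticism is narrower: the stated test is too imprecise to give that reassurance.
- **The combined analysis may sit in an analysis plan.** Table 4 covers the main outcomes and allows exploratory additions, so silence on a joint ID-ED and control-task contrast does not show that none will be done. This answers the analysis half of the point. It does not answer the missing pre-dose score or the fixed order.
- **The practice gain is unknown.** A reader might take 24.7% to 92.4% as the trial's actual false-positive rate. The article reports no ID-ED retest gain, at 34 days or any other interval, so these figures show sensitivity to an assumption.
- **The symptom claim.** A reader might extend the point to the statement in the Conclusions that "The results will reveal whether a low-moderate dose of psilocybin improves clinical OCD symptoms". That concerns Y-BOCS, which has pre-dose scores in Table 3 and a mixed model in Table 4. It is not evidence about ID-ED practice.
- **This is feasibility work.** The study is presented as preliminary and meant to guide a later trial, and the Table 2 hypothesis does literally describe the contrast tested. This lowers the severity. It does not remove the need to say what the contrast contains, because ID-ED is a primary outcome with a directional dose hypothesis.

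**Conclusion.** The point holds as a limit on interpretation. The primary ID-ED comparison measures 10 mg at the second session against 1 mg at the first, and it cannot attribute the difference to dose alone. That follows from the fixed order and the two post-dose tests, and needs no numerical assumption.

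The size does need assumptions. Practice gains of 0.3 to 0.8 SD of the paired differences, with no drug effect and a two-sided 5% test at 20 completers, would give rejection rates of 24.7% to 92.4%. The control-task half-width of 0.47 SD depends only on n = 20 and the 95% level.

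The documents do not support saying that a practice gain is present, that a null control result will be read as absence of an order effect, or that the study is invalid for its feasibility purpose. Rating: should-fix.

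**What to change.** **(a) Wording.** Restate the ID-ED hypothesis and its interpretation as a second-session (10 mg) versus first-session (1 mg) difference that combines dose and order. Add fixed order to the limitations beside sample size. This costs nothing beyond a more modest claim.

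**(b) Sensitivity analysis on data already planned.** Report the within-person standardised ID-ED change minus the standardised paired-associates change, with its 95% confidence interval, beside the primary paired difference. Name the standardising SD. State that the contrast assumes similar practice gains on two tasks that test different abilities, which these data cannot verify. The cost is precision. If each change is divided by its own SD of differences (treated as known) and the changes correlate at r, the half-width is 0.468 × √(2(1 − r)): 0.66 at r = 0, 0.55 at r = 0.3 and 0.47 at r = 0.5.

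**(c) Optional, if enrolment allows.** Give the battery once before dosing, with parallel stimuli, so that the first-exposure gain falls ahead of the dose contrast. In-person screening, where vLTP already has a baseline, or V2 is preferable to V3. V3 (D-7) is only 3 days before V6 (D-10), against 34 days from V6 to V12, and such uneven spacing could favour the 1 mg score. V2 (D-1) is 9 days before V6. Screening is at least 14 days before the first dosing day, so at least 16 days before V6. The costs should be disclosed: added burden, possible loss of task novelty and hence of sensitivity to a drug effect, and no removal of elapsed-time or support effects.

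No change to the order of doses is proposed.

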## Materials and methods

Our primary outcomes investigate a) cognitive features of OCD through the CANTAB intradimensional-extradimensional (ID-ED) task, which assesses attentional ‘set-shifting’ and b) neuroplasticity through the visual long-term potentiation (vLTP) EEG paradigm. This feature of cognition is impaired in OCD and unaffected relatives, framing it as a potential cognitive endophenotype. OCD symptoms will also be measured using the Y-BOCS, and depression scores - accounted for by the Montgomery-Asberg Depression Rating Scale (MADRS) - will also be collected. Further investigations will include self-reported psychological questionnaires designed to assess participants’ affective symptoms, including measures of anxiety, as well as their perception of the subjective psilocybin experience. The complete list of outcomes is presented in the 'outcome measures' section.

Recruitment

We will recruit up to 20 completing participants with OCD as defined by the DSM-5 criteria (assessed using the Mini-International Neuropsychiatric Interview (MINI)). Study completion is considered the fulfilment of the final study visit. Recruitment will occur via flyers, word-of-mouth, and from a pool of self-referrals submitted via a secure centralised e-mail address using a standardised referral form. Summarised participant information sheets will be openly accessible on our study website. Primary care providers will be contacted to confirm eligibility. Full entry criteria are outlined in Table 1 below.

**Table 1 TAB1:** Key PsilOCD inclusion and exclusion criteria *Antipsychotic medications may attenuate the effects of psilocybin, and limited available evidence suggests that mood stabilisers like lithium may interact with psilocybin and lead to untoward side effects [72,73]. In this population, people may be using these medications as adjunctive treatments alongside SSRIs. OCD: Obsessive-compulsive disorder; SSRI: Selective serotonin reuptake inhibitor; ERP: Exposure-response prevention

Category	Inclusion Criteria	Exclusion Criteria
Demographics	- Aged 20 to 65 years; - Any gender	- People who are pregnant, planning to get pregnant, or currently breastfeeding
Mental Health	- Primary diagnosis of OCD; - Experienced OCD for at least 12 months	- Current or previously diagnosed psychotic disorder, bipolar disorder, or mania; - Immediate family member with a diagnosed psychotic disorder; - History of serious suicide attempts (requiring hospitalisation)

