Plasticity via LTP Paradigm (EEG)	Screening vs 1 mg vs 10 mg (ANOVAs + paired t-tests or equivalent)
Predictive Processing via MMN (EEG)	Screening vs 1 mg vs 10 mg (ANOVAs + paired t-tests or equivalent)
Secondary Outcome Measures	
Reversal Learning Task (CANTAB)	Two days post DD1* vs two days post DD2** (paired t-tests or equivalent)
Paired-Associates Control Task (CANTAB)	Two days post DD1 vs Two days post DD2 (paired t-tests or equivalent)
Information-Seeking Task	One day post DD1 vs One day post DD2 (paired t-tests or equivalent)
Y-BOCS and MADRS	Linear mixed effects model (or equivalent) to test the interaction effect between time and dose (1 mg vs 10 mg) on Y-BOCS and MADRS scores.
Bloods: Plasma BDNF and Immune Factor Levels	DD1 vs DD2 (paired t-tests or equivalent)
Acute Measures (Self-Reported)	DD1 vs DD2 (paired t-tests or equivalent)
Self-Reported Well-Being and Affective Measures	Linear mixed effects model (or equivalent) to test the interaction effect between time and dose (1 mg vs 10 mg) on questionnaire scores.

Investigational medicinal product management

A Schedule 1 licence for the possession and storage of psilocybin has been obtained from the UK Home Office. Psilocybin will be supplied by COMPASS Pathways Ltd. Manufacture and encapsulation will be performed by Lonza Pharma and Biotech. Good Manufacturing Practice (GMP) will be maintained at all stages of manufacture. The investigational medicinal product (IMP) will be stored in a secure safe at Imperial College London, Hammersmith Campus.

Data management

Data will be managed as per the Imperial College Data Management Standard Operating Procedures and a study-specific data management plan. All data collection and management software has met the General Data Protection Regulation (GDPR) standards and has been approved by Imperial College London.

Dissemination

The findings of this study will be published in academic journals and shared across both academic and public platforms, including scientific conferences and public engagement forums in the media. Patient confidentiality will be upheld in all instances. All study-related publications and presentations will be managed by the Principal Investigator and Chief Investigator.

Ethics and trial registration

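### Table 4 makes mismatch negativity a third primary outcome and tests vLTP across three sessions, whereas the methods and Table 2 give two primaries and one vLTP contrast, 10 mg versus 1 mg

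*Protocol article*

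**What the plan says.** **Which outcomes are primary.** The abstract says that the "primary outcomes include scores in the intradimensional-extradimensional (ID-ED) shift task" and "neuroplasticity as quantified by a visual long-term potentiation (vLTP) task". The opening of Materials and methods gives a lettered list of two: "Our primary outcomes investigate a) cognitive features of OCD through the CANTAB intradimensional-extradimensional (ID-ED) task" as item a, and "neuroplasticity through the visual long-term potentiation (vLTP) EEG paradigm" as item b. Table 2 (Outcome measures) has two primary rows, one clinical (ID-ED) and one neuroimaging (vLTP). Table 4 (Analysis strategy), which is presented as the clear statement of the main outcomes, has three rows above its secondary heading: ID-ED, vLTP and "Predictive Processing via MMN (EEG".

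**How they are tested.** Table 2 states the vLTP hypothesis as one comparison: "Participants will demonstrate higher capacity for neural plasticity two hours post 10 mg dose compared to the 1 mg dose". Table 4 gives the same entry for both EEG rows: "Screening vs 1 mg vs 10 mg (ANOVAs + paired t-tests or equivalent". For ID-ED, the two tables agree on a single comparison, two days after 1 mg against two days after 10 mg.

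**The concern.** There are two mismatches, both visible in the article.

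First, the set of primary outcomes depends on which section is read. Mismatch negativity (MMN) appears in the Table 3 schedule at all three EEG sessions, but it has no hypothesis in Table 2 and no description under the mechanistic neurophysiology outcomes. If it is reported as primary, no stated direction or contrast exists to judge it against. If it is not, Table 4 is wrong. The article says that later papers will report in line with the stated outcomes, so readers need to know which those are.

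Second, the vLTP analysis does not match the vLTP hypothesis. Screening is an undosed visit at least two weeks before the first dose. A three-level omnibus test asks whether any of the three sessions differ, which is a different question from whether 10 mg differs from 1 mg. Because Table 4 names no decisive comparison, a significant ANOVA or a significant screening contrast could be presented as a positive primary result without any dose effect.

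**Working it through.** **Step 1. Primary outcomes by location.**

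| Place | ID-ED | vLTP | MMN |
|---|---|---|---|
| Abstract | primary | primary | not named |
| Materials and methods, items a and b | primary | primary | not named |
| Table 2 | primary, with hypothesis | primary, with hypothesis | no row |
| Table 4 | primary | primary | primary |

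MMN stands above the secondary heading in Table 4, so this is not an effect of table layout.

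**Step 2. Can the omnibus test reject with no dose effect?** The article gives no alpha, variance or correlation, so there is no stated figure to reproduce and the following is an illustration.

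- From the article: n = 20 completers, three sessions.
- Assumed: two-sided 5%; normal data with equal variances and correlation 0.5 between sessions; equal means at 1 mg and 10 mg (so no effect of session order either); screening shifted by δ SD.

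For session means (δ, 0, 0), the sum of squared deviations from their mean is (2/3)δ². The repeated-measures F test has 2 and 38 degrees of freedom, critical value 3.245 and noncentrality

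λ = n × (2/3)δ² / (1 − correlation) = 20 × (2/3)δ² / 0.5.

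| δ (SD) | λ | Omnibus rejects | Direct 10 mg vs 1 mg t-test rejects |
|---|---|---|---|
| 0.3 | 2.40 | about 25% | 5% |
| 0.5 | 6.67 | about 60% | 5% |
| 0.8 | 17.07 | about 95% | 5% |

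Simulation agrees (24% to 25%, 59% to 60%, 95%). The result depends on the correlation: at δ = 0.5 it is about 45% with correlation 0.3 and 83% with correlation 0.7.

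**Step 3. What the number of primaries does.** Assume 5% per test, independent outcomes, one test each, and that any one success would be claimed. The chance of at least one false-positive primary is 1 − 0.95^k:

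- two primaries: 1 − 0.95² = 9.75%;
- three primaries: 1 − 0.95³ = 14.3%.

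At an assumed correlation of 0.6 between outcomes, simulation gives about 9% and 12%. Two other readings of Table 4, with three primaries, independent outcomes and n = 20:

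- ANOVA first, then only the 10 mg versus 1 mg contrast for each EEG measure: just under 10%;
- all three pairwise tests for each EEG measure with no ANOVA gate, plus ID-ED (seven tests): 27% to 28%.

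**Step 4. Cost of a stricter step.** For a paired t-test with n = 20, the noncentrality is d√20, where d is the mean difference in SDs of the differences. At two-sided 0.05 (critical t 2.093), d = 0.66 gives 80% power. At 0.025 (critical t 2.433), 80% power needs d = 0.74.

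**The case against.** The strongest defence is that the two tables are compatible: Table 2 gives the hypothesis and Table 4 the sessions analysed. The paired t-tests in Table 4 include 10 mg versus 1 mg, and pairing an ANOVA with t-tests may simply mean an overall test followed by post-hoc comparisons. A significant ANOVA becomes a false dose claim only if someone reads it as one. This has force. It removes the mismatch only if the 10 mg versus 1 mg comparison is named as decisive, and Table 4 does not name it. It does nothing for MMN.

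The abstract's verb is also not strictly exhaustive, and Table 2 is titled a summary. The lettered pair in the methods still conflicts with Table 4.

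A reader might go further and infer that the trial has no control of its error rate, that it runs seven primary t-tests at 5% each, and that its false-positive rate is therefore near 28%. The article does not support that. It states no alpha, no number of pairwise tests and no rule that any one result counts as success. The gated reading in Step 3 gives just under 10%. Multiplicity rules commonly sit in an analysis plan, which is not shown, so their absence here is not a finding.

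Finally, the screening shifts and the correlation in Step 2 are assumed, and detecting a real screening difference is not in itself an error. The figures show only that the omnibus test does not answer the stated question. The article also describes a feasibility study and concedes limited power, which lowers the stakes.

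**Conclusion.** The concern holds in limited form. The contradiction over MMN is in the text and needs no assumption. An unseen analysis plan could choose between the two versions but would not make the article consistent. The vLTP mismatch is also in the text: one stated contrast in Table 2, a three-session analysis with no decisive contrast in Table 4. Under the assumptions in Step 2, the omnibus test rejects in about 25% to 95% of trials with no dose effect, against 5% for the direct contrast.

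The ID-ED primary is not affected, since its contrast is the same in both tables. It would be too strong to say that the primary claims as a whole are unfixed. The family-wise figures of about 9.8% (two primaries) and 14.3% (three) hold only at an assumed 5% per test with independent outcomes and any single success claimed; 27% to 28% is an upper case. In a feasibility study this is a correction that should be made before analysis, and it does not undermine the design.

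**What to change.** 1. In Table 4, move MMN to the secondary or exploratory outcomes so that the table agrees with the methods and Table 2. Declaring MMN primary throughout, with a hypothesis, would also be consistent, but it adds a third primary to a study of 20 completers.
2. In the vLTP row, name the paired 10 mg minus 1 mg difference as the primary test, and label the omnibus ANOVA and all comparisons with screening as supportive.
3. State whether success needs both primaries or either one. If either alone may be claimed, Holm across ID-ED and vLTP at two-sided 5% is a suitable rule, unless the analysis plan already sets one.

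Items 1 and 2 are changes of wording: no data, visit or procedure alters. Item 3 has a small cost if Holm is used: the smaller p-value must pass 0.025, and at that step the effect detectable with 80% power at n = 20 rises from about 0.66 to 0.74 SD of the differences.
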